## Assignment of interventions: randomisation

### Sequence generation: who will generate the sequence {21a}

The random allocation sequence will be generated by [name] using a computer-generated random-number algorithm. The sequence generator will not be involved in participant enrollment or group assignment.

### Sequence generation: type of randomisation {21b}

Participants will be randomly allocated to one of three study arms in a 1:1:1 ratio using restricted randomisation with permuted blocks (variable block sizes). Randomisation will be stratified by study site (two hospitals) and sex (male/female). To reduce predictability, details of block sizes will be stored in a separate document that is not accessible to personnel who enroll participants or assign interventions.

### Allocation concealment mechanism {22}

Allocation will be concealed using sequentially numbered, opaque, sealed envelopes prepared for each stratum (site × sex). Envelopes will be tamper-evident and stored securely at each recruiting site under the custody of an allocation administrator who is not involved in participant enrollment or outcome assessment. The next envelope in sequence will be opened only after participant eligibility is confirmed and baseline assessments have been completed.

## Assignment of interventions: blinding

### Who will be blinded {24a}

Blinding will be maintained using coded intervention labels (Programme A/B/C) and role separation. Participant-facing materials will use programme codes only. Screening personnel and outcome data collectors will be separate from intervention providers and will not have access to the allocation codebook. Biological samples and datasets will be labelled with study IDs only. Participants will be reminded not to disclose intervention details to blinded staff.

### How will be blinding be achieved {24b}

Blinding will be maintained through role separation and coded intervention labels. The three interventions will be presented as coded nutrition programmes (e.g., Programme A/B/C), and all participant-facing materials will use these codes. Allocation information will be accessible only to the intervention delivery team via an allocation codebook; recruitment staff, assessors, laboratory personnel, and statisticians will not have access. Participants will be reminded not to disclose details of their dietary programme to blinded staff.

### Procedure for unblinding if needed {24c}

Unblinding will be permissible only when knowledge of the assigned intervention is essential for clinical management or participant safety. Any request for unblinding will be authorised by the principal investigator, and the allocation will be revealed by the intervention delivery team using the allocation codebook. The reason, date, personnel involved, and the participant(s) unblinded will be documented. Outcome assessors will remain blinded whenever possible.

### Plans to promote participant retention and complete follow-up {25b}

To promote retention and complete follow-up, participants will receive enrollment education and written materials (brochures) and will be reminded of scheduled assessments via WeChat messages, reminder cards, and telephone calls. Whenever possible, follow-up will be aligned with routine chemotherapy-related contacts, with flexible scheduling within predefined visit windows. Missed visits will trigger repeated contact attempts, and reasons for missed visits, discontinuation, or protocol deviations will be documented. Participants who discontinue or deviate from the allocated dietary intervention will be encouraged to remain in follow-up; every reasonable effort will be made to collect key outcome and safety data at the scheduled time points to support intention-to-treat analyses. If a participant withdraws consent for further data collection, no additional data will be collected, and the withdrawal reason will be recorded if the participant agrees.

## Statistical methods

### Statistical methods for primary and secondary outcomes {27a}

Analyses will be prespecified in the statistical analysis plan (SAP) and conducted using R and/or SPSS. Baseline characteristics will be summarized by group using mean ± SD or median (IQR) for continuous variables and n (%) for categorical variables. Two primary comparisons will be performed: plant-based diet versus conventional diet, and plant-based diet versus conventional diet plus oncology nutritional formula. To control the family-wise type I error across the two primary comparisons, we will use a Bonferroni-adjusted two-sided α of 0.025 for each comparison [26]. Within each comparison, the three co-primary outcomes will be tested using a pre-specified hierarchical gatekeeping procedure in the following order: (1) CIGT, (2) serum inflammatory biomarkers, and (3) stool-based multi-omics. For the confirmatory test of the first co-primary outcome (CIGT), the primary clinical endpoint is the participant-level incidence of experiencing any prespecified CTCAE gastrointestinal toxicity of grade ≥ 2. Testing will proceed to the next outcome only if the preceding outcome is statistically significant at the same two-sided α level; otherwise, subsequent outcomes will be analysed and reported as supportive/exploratory without confirmatory claims.

The confirmatory analysis of the primary clinical endpoint will use logistic regression with adjustment for the stratification factors (site and sex) and other prespecified covariates as applicable. Longitudinal continuous outcomes will be analysed using linear mixed-effects models with fixed effects for group, time, and group-by-time interaction and a participant-level random intercept (and random slope if supported), adjusting for the baseline value of the outcome (when applicable) and the stratification factors. Longitudinal ordinal CTCAE grades and time-specific binary indicators (e.g., grade ≥ 2 at each time point) will be analysed as key secondary/supportive outcomes using mixed-effects ordinal logistic models and mixed-effects logistic regression, respectively, with the same covariate structure.

Microbiome and metabolomics outcomes will be analysed according to prespecified metrics. For metabolomics, multivariate structure will be explored using ordination, and feature-level differences over time will be tested using regression/mixed-effects frameworks with false discovery rate (FDR) control; pathway-level enrichment analyses will be reported as supportive. Community-level differences will be assessed using distance-based methods, and feature-level analyses will apply appropriate regression frameworks with FDR control for multiple testing. Harms events will be summarized by group (incidence, severity, seriousness, and relatedness) and compared using χ^2^/Fisher’s exact tests or regression models as appropriate; serious adverse events and events leading to intervention discontinuation will be described descriptively.

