### Sample size {19}

Sample size was estimated using the Tests for Two Proportions module in PASS 2025 for the primary endpoint, defined as experiencing any prespecified CTCAE gastrointestinal toxicity of grade ≥ 2. Given two prespecified primary comparisons, a Bonferroni-adjusted two-sided α of 0.025 and 80% power were applied. Based on Souza et al. [24], the assumed proportions were 0.176 in the intervention group and 0.533 in the control group. Under these assumptions, 30 evaluable participants per group are required for each primary comparison. To account for an anticipated 20% loss to follow-up, this was rounded up to 38 participants per arm (total N = 114; 1:1:1).

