## Discussion

This multicentre, stratified, three-arm randomised controlled trial is designed to evaluate the efficacy and safety of a structured plant-based dietary strategy for mitigating CIGT during FOLFOX chemotherapy in patients with CRC, compared with conventional dietary guidance with or without an oncology nutritional formula. In addition to repeated clinical assessments of gastrointestinal toxicity, the trial will collect inflammatory biomarkers and stool-based multi-omics data to support exploratory investigation of biological correlates of symptom burden and treatment tolerance.

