This protocol has several strengths. The three-arm design uses clinically relevant comparators that reflect real-world nutritional management during chemotherapy and allows separation of effects attributable to a structured dietary pattern from those related to nutritional supplementation alone. Stratified randomisation by site and sex improves balance for key prognostic factors, and repeated measurements across the intervention window support evaluation of symptom trajectories rather than reliance on a single endpoint. The integration of clinical endpoints with inflammatory biomarkers and stool-based profiling provides an opportunity to generate mechanistic hypotheses and to identify candidate signatures associated with symptom severity or response, while the use of prespecified analytical approaches (including appropriate control for multiple testing in high-dimensional data) supports transparent interpretation.

There are several limitations to consider. Although participant blinding will be attempted using coded programmes and role separation, it may not be fully maintained in food-based interventions due to recognisable differences in dietary content and delivery. The follow-up period is limited to six weeks and may not capture longer-term effects beyond the planned window. Multi-omics analyses are exploratory and high-dimensional; findings will require cautious interpretation and independent validation. Generalizability may also be constrained by eligibility criteria and recruitment from two hospitals in one region, which may under-represent older patients, those with severe malnutrition, or patients receiving alternative chemotherapy regimens.

If the intervention demonstrates clinically meaningful reductions in CIGT with acceptable safety, the results will support the use of a structured plant-based dietary strategy as an adjunct to standard supportive care during FOLFOX chemotherapy and inform scalable implementation pathways in routine oncology practice. Even if effects are modest, the trial will provide valuable feasibility information on adherence, retention, specimen completeness, and operational barriers that can guide refinement of dietary delivery models and the design of larger, longer-term confirmatory trials.

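### The two comparisons never share alpha, so the 0.025 left over when one comparison's whole test chain succeeds is discarded; passing it on would cost nothing and gain a modest amount of power

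*Protocol article*

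**What the plan says.** Statistical methods {27a} names the comparisons: "Two primary comparisons will be performed: plant-based diet versus conventional diet, and plant-based diet versus conventional diet plus oncology nutritional formula". On error control it says "To control the family-wise type I error across the two primary comparisons, we will use a Bonferroni-adjusted two-sided" level of 0.025 for each. Inside a comparison, "Within each comparison, the three co-primary outcomes will be tested using a pre-specified hierarchical gatekeeping procedure in the following order": CIGT, then serum inflammatory biomarkers, then stool multi-omics. The rule for moving on is "Testing will proceed to the next outcome only if the preceding outcome is statistically significant at the same two-sided α level". So each comparison's full 0.025 travels down its own three steps. No sentence sends any of it to the other comparison, whatever is rejected.

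Sample size {19} uses the same level: "a Bonferroni-adjusted two-sided α of 0.025 and 80% power were applied". It assumes event proportions of 0.176 (intervention) and 0.533 (control), giving 30 evaluable and 38 randomised per arm, 114 in total. One control proportion is given, with no separate figure for the formula arm.

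The Discussion bears on what the last step protects: "Multi-omics analyses are exploratory and high-dimensional".

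**The concern.** When all three steps of one comparison are rejected, that comparison has no further use for its 0.025, yet the other comparison's CIGT test stays at 0.025. A p-value between 0.025 and 0.05 there is then declared non-significant although the overall 0.05 budget would allow the claim. Winning both CIGT comparisons matters in this trial, because the formula arm was included to separate the effect of the diet from that of supplementation (Explanation for the choice of comparator {9b}). With 30 evaluable participants per arm, power to win both is well below the 80% planned for each comparison.

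**Working it through.** **1. The plan's own figure.** Two proportions, unpooled variance, two-sided 0.025, 80% power:

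n = (2.2414 + 0.8416)² × (0.176×0.824 + 0.533×0.467) / (0.533 − 0.176)² = 9.505 × 0.3939 / 0.1274 = 29.4, so 30. Then 30/0.8 = 37.5, so 38, and 3 × 38 = 114. The stated numbers reproduce.

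**2. Error control when alpha passes at the end of a chain.**
- If both chains contain a true null, neither can be completed without an error already having been made. The first error must therefore occur at 0.025 in one chain or the other, and family-wise error is at most 0.025 + 0.025 = 0.05.
- If only one chain contains a true null, that null is tested at 0.05 at most.

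Either way the limit is 0.05. This needs each step to be one test, or one family-wise-controlled set of tests.

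**3. The two ends of the scale.** Exact binomial enumeration with the shared plant-based arm, 30 per arm, pooled Z, power to win both CIGT comparisons. The formula-arm rates of 0.40 and 0.30 are assumptions.

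| Formula-arm rate | Plan as written | Full Holm on CIGT | Difference |
|---|---|---|---|
| 0.533 | 64.7% | 73.7% | 8.9 points |
| 0.40 | 35.3% | 45.2% | 9.9 points |
| 0.30 | 12.7% | 19.1% | 6.4 points |

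(Differences are taken before rounding.) At 0.533 the chance of at least one CIGT win is 89.5% under either rule. The choice of test shifts the levels: for both wins at 0.533, unpooled Z goes from 67.9% to 76.2% and Fisher from 50.8% to 63.2%.

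**4. End-of-chain passing lies between them.** An extra double win needs one CIGT p-value at or below 0.025, the other between 0.025 and 0.05, and the remaining steps of the first chain all rejected. Let q be the probability of that last condition, assumed equal for both comparisons and independent of CIGT:

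power(both) = power(plan) + q × [power(Holm) − power(plan)].

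The protocol gives no power for biomarkers or omics. The assumed ranges are 50–80% and 30–80%, so
- with omics in the chain, q runs from 0.5×0.3 = 0.15 to 0.8×0.8 = 0.64;
- with the chain ending at biomarkers, q runs from 0.50 to 0.80.

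| Formula-arm rate | Plan | Passing, omics in chain | Passing, chain ends at biomarkers |
|---|---|---|---|
| 0.533 | 64.7% | 66.1–70.4% | 69.2–71.9% |
| 0.40 | 35.3% | 36.8–41.6% | 40.2–43.2% |
| 0.30 | 12.7% | 13.7–16.8% | 15.9–17.8% |

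For example, 64.7 + 0.15×8.9 = 66.1 and 64.7 + 0.64×8.9 = 70.4.

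**5. Why Holm cannot simply be added.** Suppose CIGT truly differs in comparison 1 and is rejected, while comparison 1's biomarkers and comparison 2's CIGT are null. Holm with the present gate kept would test those nulls at 0.025 and 0.05. Family-wise error is 1 − 0.975×0.95 = 0.0738 if independent, 0.069 at correlation 0.5 (simulation), and at most 0.075. The plan as written gives 1 − 0.975² = 0.0494.

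**6. What a valid Holm version costs.** Suppose biomarkers open only after both CIGT wins. The gate to the plant-based versus conventional biomarker test then opens in 74% of trials instead of 77% at a formula-arm rate of 0.533, but in 19% instead of 77% at an assumed 0.30.

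**The case against.** The strongest reply is that nothing here is wrong. The two sections agree, error is controlled, and the alpha is not idle: after a CIGT win it funds the biomarker test and then the omics test of the same comparison. All of that stands, so this is an efficiency refinement and not an error.

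A reader might go further and infer that the full Holm gain is available free of charge. The documents do not support that. The alpha Holm would release after a CIGT win is already committed to that comparison's biomarkers. Taking it means giving up or restricting those claims, or exceeding 0.05.

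A reader might also infer that the biomarker step protects no real claim, since the Discussion says "the trial will collect inflammatory biomarkers and stool-based multi-omics data to support exploratory investigation of biological correlates". That sentence concerns correlates of symptom burden and treatment tolerance, not the between-arm biomarker test. The Abstract, the Objectives {10}, the Outcomes {16} and {27a} all place serum biomarkers among the primary outcomes. Only multi-omics is itself called exploratory.

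It is also fair to object that the gain is small and depends on unstated power for the later steps. That stands, and is why the result is given as a range.

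**Conclusion.** The rule in {27a} is valid and matches the sample size, but it discards 0.025 whenever one comparison's chain is fully rejected. Recovering it is never worse and loses no claim. The gain is modest. At 30 per arm, pooled Z and 0.533 in both comparators, power to win both CIGT comparisons goes from about 65% to about 66–70%, or about 69–72% if the chain ends at biomarkers. These figures rest on the assumed later-step powers and on their independence from CIGT. With the later-step powers held fixed, the absolute gain is similar at an assumed formula-arm rate of 0.40 and smaller at 0.30. The chance of at least one CIGT win is unchanged.

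**What to change.** Keep both chains at two-sided 0.025. Add to {27a} and the SAP that, once every confirmatory step of one comparison has been rejected, its 0.025 passes to the other comparison, whose chain from CIGT onward is then tested at 0.05. Define each confirmatory step as a single family-wise-controlled test; this includes the biomarker step, which covers at least IL-6 and CRP.

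Optionally, end the confirmatory chain at serum biomarkers and report multi-omics as exploratory. That fits the Discussion and makes the passing more useful, at the price of a confirmatory omics claim.

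Full Holm on the two CIGT tests is an alternative only if the sponsor accepts biomarkers as supportive, or opened after both CIGT wins. It must not be combined with the current 0.025 gate.

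The cost is wording: a protocol amendment and the matching SAP text, with no extra patients or data. There is time. Trial status reports 7 participants enrolled as of 23 January 2026, and the SAP is due to be finalised before database lock and unblinding.

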#### Secondary outcomes

Dietary assessment: Dietary assessment will be conducted using a semi-quantitative FFQ and diet records (food diaries). The FFQ will capture usual dietary intake over the preceding week, including consumption frequency and portion size, and will be administered at T0 and T7. FFQ data will be used to derive plant-based diet indices [Plant-Based Diet Index (PDI), healthy Plant-Based Diet Index (hPDI), and unhealthy Plant-Based Diet Index (uPDI)] by applying pre-specified scoring to plant- and animal-food groups, adapted to the Chinese Dietary Guidelines and the study intervention targets [17]. Diet records will prospectively document all foods and beverages consumed over three consecutive days at a randomly selected time during the intervention period (T0-T7). Outcomes will be summarised as index scores at each FFQ time point and change from T0 to T7, and as average daily intake estimates from the 3-day records (reported as mean ± SD).Nutrition assessment: Nutritional status will be evaluated using bioelectrical impedance analysis [Bioelectrical Impedance Analysis (BIA)] and routinely collected clinical laboratory tests at prespecified time points. BIA will be performed with the InBody 370 at T0 and T7 by trained study staff using a standardised procedure [20], yielding body weight and body-composition measures (e.g., fat mass, fat-free mass, skeletal muscle mass, and segmental composition in appendicular and trunk compartments). Routine blood tests will be extracted from the hospital laboratory information system at T0, T3, T5, and T7. Prespecified laboratory domains include nutrition-related markers, lipid and glucose profile, liver and renal function indices, immune cell counts, and tumour markers (Table 1). Outcomes will be summarised as values at each time point and as change from T0 (reported as mean ± SD).Fatigue: Fatigue will be assessed using the Chinese version of the Piper Fatigue Scale-12 (PFS-12) [21], a 12-item self-report instrument covering four dimensions (behavioural, affective, sensory, and cognitive). Each item is rated on a 0–10 numeric scale, and the total score is calculated as the mean of all 12 items (range 0–10), with higher scores indicating more severe fatigue. Assessments will be completed at T0, T3, and T7. Outcomes will be summarised as (i) the PFS-12 total score at each time point and (ii) change from T0 at each follow-up (reported as mean ± SD).Anxiety and depression: Anxiety and depression will be assessed using the Hospital Anxiety and Depression Scale (HADS) [22], a 14-item self-report instrument comprising two 7-item subscales (anxiety and depression). Items are rated on a 4-point scale, yielding subscale scores from 0 to 21, with higher scores indicating greater symptom severity. Assessments will be completed at T0, T3, and T7. Outcomes will be summarised as (i) anxiety and depression subscale scores at each time point and (ii) change from T0 at each follow-up (reported as mean ± SD).Physical activity: Physical activity will be assessed using the Chinese short form of the International Physical Activity Questionnaire (IPAQ-C) [23]. The questionnaire captures self-reported walking, moderate-intensity activity, and vigorous-intensity activity over the previous 7 days. Participants will be classified into low, moderate, or high physical activity according to the IPAQ scoring protocol. Assessments will be completed at T0, T3, and T7. Outcomes will be summarised as the proportion of participants in each physical activity category at each time point and the change in category from T0 to each follow-up (reported as n, %).

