### How missing data will be handled in the analysis {27c}

Every effort will be made to minimise missing data through the retention procedures described above. For longitudinal outcomes, mixed-effects models using maximum likelihood estimation will be the primary approach and can accommodate missing outcome data under a missing-at-random assumption. If additional handling is required (e.g., substantial missingness in key secondary outcomes), multiple imputation will be applied using prespecified models incorporating baseline variables, stratification factors, and available outcome history; results will be compared with complete-case analyses as sensitivity checks. For microbiome/metabolomics features, no imputation will be performed for unavailable samples; analyses will be based on available specimens, with missingness patterns summarized and sensitivity analyses performed where appropriate.

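### For fatigue and HADS, the default random-intercept model forces one residual variance on weeks 2 and 6, so the week-6 standard error is too small if correlation with baseline fades

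*Protocol article*

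**What the plan says.** Protocol article, {27a}, sets "linear mixed-effects models with fixed effects for group, time, and group-by-time interaction" for longitudinal continuous outcomes. The random part and the baseline adjustment are given as "a participant-level random intercept (and random slope if supported), adjusting for the baseline value of the outcome (when applicable"), together with site and sex as stratification factors. Under {27c}, "mixed-effects models using maximum likelihood estimation will be the primary approach" for longitudinal outcomes.

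Under Secondary outcomes, fatigue and HADS share one schedule: "Assessments will be completed at T0, T3, and T7". The participant timeline {18} places T3 at week 2 and T7 at week 6. Routine laboratory values are taken at T0, T3, T5 and T7. The secondary objectives in {10} compare fatigue, emotional status and laboratory measures from baseline to week 6.

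The article gives no SD, between-visit correlation or reliability for any of these outcomes. It states no reference distribution or degrees-of-freedom method for the mixed models, and no significance level for secondary outcomes.

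**The concern.** A random intercept alone implies the same residual variance at every visit. After adjustment for T0, that variance depends on how strongly each visit still correlates with T0. Week 6 is further from baseline than week 2, so it may well carry the larger residual variance even when the raw SDs are equal. The model would then average the two variances and apply the average to the week-6 contrast, which is the visit the objective names. Confidence intervals would be too narrow there and p-values too small.

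The slope clause is no clear remedy. With two responses the usual correlated slope is out of reach. With three responses (laboratory values) it can be fitted, but whether it stays is decided on the data by a criterion the article does not state. Maximum likelihood adds a small downward bias to the variances at 38 per arm.

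**Working it through.** The article states no standard error or error rate for these models, so there is no figure of its own to reproduce. Its arm size is consistent: 30 / 0.8 = 37.5, rounded up to 38, and 3 × 38 = 114.

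**1. Parameters against information.**
- T3 and T7 as responses give 2 variances + 1 covariance = 3 quantities. A correlated intercept and slope plus residual needs 4 parameters, so it is not estimable.
- An uncorrelated intercept and slope plus residual needs 3, so it is just identified.
- T0, T3 and T7 all as responses, or laboratory values at T3, T5 and T7, give 6 quantities for 4 parameters, so the correlated slope is estimable.

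**2. Standard error under a random intercept.** Let r be the week-6 residual SD divided by the week-2 residual SD, after baseline adjustment. With complete data the model uses the average of the two variances:

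model SE / true SE = √((1 + r²)/2) / r, and actual error = 2 × [1 − Φ(1.96 × that ratio)] at nominal 0.05.

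The simulation column imposes r directly: 4,000 null trials per cell, three arms of 38, residual correlation 0.3 or 0.6, 0% or 20% missing at T7, site and sex adjusted, maximum likelihood, Wald z.

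| r | SE ratio | Error, formula | Error, simulated |
|---|---|---|---|
| 0.67 | 1.27 | 0.013 | 0.013–0.017 |
| 1 | 1.00 | 0.050 | 0.056–0.060 |
| 1.2 | 0.92 | 0.071 | 0.072–0.086 |
| 1.5 | 0.85 | 0.096 | 0.101–0.113 |
| 2 | 0.79 | 0.121 | 0.130–0.145 |

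In the same runs, a week-6 ANCOVA with its own variance gave 0.042–0.062. Maximum likelihood instead of REML adds about 0.5 to 1 percentage point (0.0595 against 0.0530 in one cell at r = 1).

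**3. What r could be (assumed).** Take equal raw SDs, scaled to 1, so the residual variance at a visit is 1 − corr(T0, visit)².
- AR(1) with correlation ρ per two weeks and no measurement error: r = √((1 − ρ⁶)/(1 − ρ²)). For ρ = 0.5, √(0.9844/0.75) = 1.15. For ρ = 0.7, √(0.8824/0.51) = 1.32. For ρ = 0.9, √(0.4686/0.19) = 1.57.
- The same with reliability 0.8, so that each between-visit correlation is multiplied by 0.8: r is 1.09 to 1.19. For example, at ρ = 0.8, √((1 − 0.64 × 0.2621)/(1 − 0.64 × 0.64)) = √(0.8322/0.5904) = 1.19.
- Constant correlation: r = 1.

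**4. Error in those settings**, simulated under no effect with 38 per arm, a random intercept, maximum likelihood and Wald z:
- AR(1), 0.5 to 0.9: 0.066–0.110
- AR(1) with reliability 0.8: 0.066–0.080
- Constant correlation: 0.060
- Week-6 ANCOVA with its own variance: 0.044–0.055

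**5. When it doubles.** Setting the formula in step 2 to 0.10 gives r of about 1.56, which step 3 reaches only near ρ = 0.9 without measurement error.

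**The case against.** The best case for the plan has four parts.

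- **The structure is not fixed.** The slope is conditional, baseline adjustment applies only where applicable, and {27a} refers analyses to the SAP. A reader might infer that a random slope is impossible for fatigue and HADS. That is too strong: an uncorrelated slope is just identified with two visits. At ρ = 0.9, an intercept variance of 0.049, a slope variance of 0.0087 and a residual of 0.106 reproduce the assumed covariance: 0.049 + 4 × 0.0087 + 0.106 ≈ 0.19 and 0.049 + 36 × 0.0087 + 0.106 ≈ 0.468. Keeping T0 as a response also makes a correlated slope estimable. This stands. The text selects neither route, however, so the default remains the random intercept.
- **The variance pattern is assumed.** Nothing in the article shows a larger week-6 residual variance, and the reverse pattern makes the test conservative. This stands. A correlation that fades with time is an ordinary expectation, but it is not a documented fact.
- **AR(1) without measurement error is unrealistic for self-report scales.** This largely stands, and reliability 0.8 brings the error down to about 0.065 to 0.08. The Wald z reference is likewise an assumption of the check.
- **Covariance detail belongs in the SAP.** Partly. Silence on degrees of freedom is no fault in an article. But the article does name a random-effects structure and an estimator, and those stated choices are what the point concerns.

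**Conclusion.** The point holds conditionally. For PFS-12 and HADS, with T0 as covariate, the stated default imposes equal residual variance at weeks 2 and 6. If correlation with baseline fades, the nominal 0.05 error at week 6 is about 0.065 to 0.11 (1.3 to 2.2 times nominal) over AR(1) 0.5 to 0.9, and about 0.065 to 0.08 with reliability 0.8. Under constant correlation it is about 0.06, from maximum likelihood with a z reference alone. With a smaller week-6 variance it falls below 0.05. For laboratory values, the flaw is a data-dependent choice of slope.

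A reader might infer that false positives roughly double. The documents do not support that: doubling is the top of an assumed range. Nor does the point reach the confirmatory claim. The CIGT test is a logistic regression, and IL-6, CRP, FFQ and BIA outcomes have a single follow-up value, so no variance is pooled across visits. Only fatigue, HADS and routine laboratory values are affected. All are secondary and outside the gatekeeping sequence. The change should be made, but the trial's main result does not depend on it.

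**What to change.** For fatigue, HADS and routine laboratory values, replace the random intercept with optional slope, fitted by maximum likelihood, with a repeated-measures model:
- visit as a category, arm-by-visit, baseline-by-visit, site and sex;
- unstructured within-participant covariance, REML and Kenward-Roger degrees of freedom;
- the arm contrast at T7 named as the estimate;
- one covariance structure fixed in advance as the fallback if the model does not converge, in place of the conditional slope.

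This keeps the error near nominal whichever way the variance moves. The cost is wording in {27a}, {27c} and the SAP, which {5} says will be finalised before database lock. Statistically it costs a few more covariance parameters and, where week-6 variance is larger, slightly wider intervals.
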